### Withdrawal and discontinuation

Participants can withdraw voluntarily at any time during the trial. Participants who are unable to complete the study, regardless of time or reason, are considered dropouts. The last recorded data for these participants will be included in the data analysis.

Withdrawal due to adverse events is distinguished from withdrawal due to inadequate response. All adverse effects are analyzed at the study endpoint regardless of whether they are considered relevant to the study treatment or not. If a participant withdraws due to a serious adverse event, it will be reported according to the reporting requirements. Where appropriate, data collected by these participants will be used in intention-to-treat analyses.

### Data management and monitoring

Study data will be collected in the CRF by clinical research coordinator (CRC) who carried out a Good Clinical Practice training course. No record will be missed or omitted, and the primary input of the data will not be permitted to be changed. Any corrections should be explained in the appended notes signed and dated by the researcher.

For data confidence, written data will be stored in a locked space at the study sites with access limited to the researchers. Electronic data will be stored in a password-protected computer.

Data will be double-entered. Double data entry of CRFs will be conducted by two experienced independent data entry clerks within 2 weeks of data collection. The data stored in a finalized clinical trials database will be ensured to be an accurate reflection of its source and will conform to specific standards of quality.

The study monitoring will follow Good Clinical Practice principles and will be processed by the Korean Medicine Clinical Trial Center of Kyung-Hee University. No formal data monitoring committee will be convened for this study. However, a clinical research associate (CRA) will be in attendance every 4 weeks to monitor and ensure the quality of the recorded data. The CRA will check the medical records, informed consent forms, source documents, and the CRFs.

### Statistical analysis

An independent statistician blinded to group allocation will perform statistical analysis on the full analysis set (FAS) and will also perform a per-protocol (PP) analysis. Missing data imputation (last observation carried forward [LOCF]) will be used to evaluate the robustness of the primary endpoint. The null hypothesis is that the two groups have no changes in any of the outcome variables.

The independent-samples *t* test or the Mann-Whitney test will be used to compare the primary outcomes between the two groups. For the primary outcome measure, a repeated measures analysis of variance (ANOVA) will also be used to test the effect of time and the treatment cross-effect.

For secondary outcome measures, the independent-samples *t* test or the Mann-Whitney test will be used to analyze continuous variables, and the chi-squared test to analyze categorical variables. For safety outcomes, the incidence of adverse events will be determined, and the two groups will be compared. A *P* value below 0.05 will be considered statistically significant.

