### Design and setting

This is a randomized, open-label, assessor-blind, parallel pilot clinical study. This trial will be performed at Dongguk University Ilsan Oriental Hospital in Korea. A total of 40 participants who meet the inclusion and exclusion criteria will be divided into two groups with a 1:1 allocation ratio. The control group will receive acupuncture, and the experimental group will receive electric heating moxibustion. The 8-week study period consists of a 4 week treatment phase and a 4 week follow-up phase.

Figure 1 outlines the trial procedures, and Fig. 2 shows the schedule for enrollment, intervention, and assessments. The Standard Protocol Items: Recommendations for Interventional Trials (SPIRIT) checklist is provided in Additional file 1.

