### Sample size

In the recent systematic reviews on rhinitis with acupuncture and moxibustion, there was no study that used moxibustion alone on PAR [26]. Furthermore, due to the special method of using electric moxibustion, we could not utilize the existing research, and it was necessary to have a flexible approach to statistical design with an exploratory study.

According to the suggestion of Julious [27], the appropriate sample size for a two-arm pilot study should be more than 12. Thus, considering the possibility of dropouts and the other characteristics of this pilot study, we will initially recruit 20 individuals per group.

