### Randomization and blinding

Randomization will be achieved with a computerized random number generator using the stratified block randomization method of SAS (SAS Institute, Inc., Cary, NC, USA). This will be performed by an independent statistician who is not involved in the clinical trial.

The random numbers will be concealed using sequentially numbered, opaque, sealed envelopes. The participant’s envelope is delivered to the site’s code manager. If a participant is enrolled and needs randomization, the envelope will be sent to the TKM doctor who performs the treatment. The doctor will open the envelope in front of the participant. A list of generated codes and SAS programs is kept by statisticians in case of loss.

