### Outcome assessments

#### Primary outcome

The primary outcome measure will be the change of the Total Nasal Symptom Score (TNSS) from baseline (visit 2) to the end of treatment (visit 9). The TNSS evaluates each of four symptoms (rhinorrhea, nasal obstruction, and nasal itching and sneezing) on a 4-point scale (0: no symptoms, 1: mild symptoms, 2: moderate symptoms, 3: severe symptoms], so the total score ranges from 0 to 12 [30].

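### The primary test of change in TNSS is unadjusted for baseline and strata, which can cost precision, and the t test or Mann-Whitney choice is left open against a hypothesis on means

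*Protocol article*

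**What the plan says.** The Primary outcome section of the protocol article reads: "The primary outcome measure will be the change of the Total Nasal Symptom Score (TNSS) from baseline (visit 2) to the end of treatment", which it places at visit 9. The Hypothesis section sets the null as a zero difference between the groups in mean TNSS change, against a two-sided alternative.

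For the comparison, the Statistical analysis section states: "The independent-samples *t* test or the Mann-Whitney test will be used to compare the primary outcomes between the two groups". It adds that "a repeated measures analysis of variance (ANOVA) will also be used to test the effect of time and the treatment cross-effect". No covariate is named for either analysis. The significance threshold is 0.05, and the statistician is blinded to allocation.

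The Randomization and blinding section says that the list is produced "using the stratified block randomization method of SAS". The article does not name the strata. Site cannot be one of them, because the Design and setting section gives a single hospital. On numbers, the Sample size section says "we will initially recruit 20 individuals per group", from a pilot rule of thumb plus an unquantified dropout allowance. No SD, effect size, power or baseline-to-end correlation is given.

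**The concern.** Three features of the stated primary test deserve attention.

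- **Baseline.** A change score subtracts the whole baseline value. If the regression slope of visit 9 on baseline is below 1, this over-corrects for any chance baseline imbalance and adds noise. ANCOVA estimates the slope instead.
- **Strata.** Balancing the arms on a prognostic factor and then leaving that factor out makes the standard error of the t test too large on average.
- **Choice of test.** Mann-Whitney does not in general test equality of means, and it gives no mean difference in TNSS points. With no rule for choosing, the primary result could come from either test, and the choice could be made after both are seen.

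At stake is the width of the interval around the one efficacy estimate that this pilot hands to a larger trial, and which of two tests decides whether a difference is declared.

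**Working it through.** The plan has no power calculation to reproduce. The check therefore compares the two analyses at the planned size.

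**Inputs.** n = 20 per arm (Sample size). Baseline and end of treatment are visits 2 and 9 (Primary outcome). The entry rule requires at least two symptoms scored 2 or more (Inclusion criteria), so TNSS at entry is at least 2 × 2 = 4 of 12. *Assumed, because the documents give no figure:* correlation r of 0.3, 0.5 or 0.7, and the ratio k of baseline SD to visit 9 SD, either 1 or 0.8.

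**Formulas**, with the visit 9 SD set to 1:

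- Change-score variance: 1 + k² − 2rk. For k = 1 this is 2(1 − r).
- ANCOVA variance: 1 − r², times 1 + 1/(2n − 4) = 1 + 1/36 = 1.028 for estimating the slope with 20 per arm.
- Ratio for k = 1: 1.028 × (1 + r)/2.
- Ratio for k = 0.8: 1.028 × (1 − r²)/(1.64 − 1.6r).

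**Worked at r = 0.3.** For k = 1: 1.028 × 0.65 = 0.67. For k = 0.8: 1.028 × 0.91/1.16 = 0.81.

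| Assumed r | Variance ratio, k = 1 | SE reduction, k = 1 | Equivalent n per arm under the planned test, k = 1 | Variance ratio, k = 0.8 |
|---|---|---|---|---|
| 0.3 | 0.67 | 18% | 29.9 | 0.81 |
| 0.5 | 0.77 | 12% | 25.9 | 0.92 |
| 0.7 | 0.87 | 6.5% | 22.9 | 1.01 |

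With k = 1, wherever the planned t test would have 80% power, ANCOVA would have 93%, 89% and 85%.

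**Check with the entry rule built in.** A simulation of four items scored 0 to 3 applied the entry rule at baseline, with assumed latent parameters and no strata. It gave variance ratios of 0.81, 0.92 and 0.99 (before the small-sample factor) at r = 0.30, 0.51 and 0.71. For an assumed 1.5-point difference, power for the t test against ANCOVA was 54% and 62%, 59% and 61%, and 74% and 73%. The type I error of the t test, Mann-Whitney and ANCOVA lay between 4.2% and 5.4%.

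**Chance imbalance.** The 95% range of the baseline difference is ±1.96 × √(2/20) = ±0.62 SD. What reaches the change-score estimate is (1 − slope) times that. With k = 1 the slope is r, giving 0.43, 0.31 and 0.19 SD. With k = 0.8 the slope is r/0.8, giving 0.39, 0.23 and 0.08 baseline SDs.

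**Strata.** Suppose balanced strata explained a share R² of the change-score variance. The t test would then in effect use a critical value of 1.96/√(1 − R²), and the true error would be about 3.9%, 2.8% and 1.9% at R² of 0.1, 0.2 and 0.3. These values only illustrate the direction. The strata are not named, so no R² can be taken from the documents.

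**Repeated measures ANOVA.** With only visits 2 and 9, its group-by-time test is the t test on change. The visit schedule for TNSS is in a figure that is not shown, so more visits may enter. Even so, no baseline or stratum covariate is named.

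**The case against.** The strongest reply is that an unadjusted two-sample test on change is a valid randomised comparison, and that covariates and the rule for choosing a test are often left to an analysis plan, which is not at hand. The first part stands: this is a matter of efficiency. The second stands only in part. The article does not leave the method open for later; it names the tests. A later plan that made ANCOVA primary would depart from what is published here.

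It is also fair to say that the trial is a pilot with feasibility aims and no power target. That lowers the weight of the point. But the article still states a formal hypothesis and a 0.05 threshold, and a tighter estimate would serve the planning of a larger trial.

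Blinding of the statistician limits a choice of test that favours a particular arm. It does not settle which test is primary, since the P values of both tests can be seen with the arms coded.

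A reader might infer more than the documents support:

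- *That baseline TNSS is ignored.* It is not; it is subtracted.
- *That the planned test is biased or inflates false positives.* It is unbiased over randomisation, and leaving out prognostic strata makes it conservative.
- *That a definite power gain or a definite type I error can be quoted.* Both need an effect, an SD, a correlation or a stratum R² that the documents do not give. The entry rule may remove most of the gain.
- *That adjustment is free.* Each covariate term uses a degree of freedom, which counts with 40 patients.

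**Conclusion.** The point holds as a moderate one about precision and prespecification. The planned comparison is valid but can be less precise than a baseline-adjusted one. Depending on the assumed correlation and SD ratio, the saving in variance at 20 per arm runs from about a third (r = 0.3, equal SDs) to nothing (r = 0.7, baseline SD 0.8 of the visit 9 SD). How far the entry rule narrows the baseline SD is itself an assumption. The loss from omitting strata has a known direction and an unknown size.

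The mismatch between Mann-Whitney and the hypothesis on mean change, and the lack of a rule for which test is primary, rest on the text alone and need no assumption.

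**What to change.** In the Statistical analysis section, replace the either-or wording with one primary analysis: ANCOVA of visit 9 TNSS on treatment, baseline TNSS and the stratification factors, reporting the adjusted mean difference with its 95% CI. Name the factors there and keep them few, given 40 patients at one site. Keep Mann-Whitney on the change score as a sensitivity analysis. Use the same baseline-adjusted model for the continuous secondary outcomes.

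The cost is a change of wording made before unblinding, plus one degree of freedom per covariate term. With treatment and baseline TNSS in the model, 37 residual degrees of freedom remain at full recruitment (40 − 3), against 38 for the t test. No further data are needed, because the baseline score is already collected and the strata are known from randomisation.

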### Ethics

The protocol complies with general ethical guidelines (the Declaration of Helsinki and Korean Good Clinical Practice), was approved by the institutional review board of Dongguk University Ilsan Oriental Hospital, and was registered at ClinicalTrials.gov (NCT03342105). Prior to onset, all participants will be informed of the methods of the trial, including possible benefits and adverse events, and their responsibilities. All enrolled subjects will voluntarily enter the study and will provide written informed consent prior to participation.

## Discussion

AR is a common disorder that interferes with the daily activities and reduces the quality of sleep of an affected individual, and it is also a significant societal burden [5]. We chose to study individuals with PAR because generally symptoms of PAR are more severe than those of SAR [35] and because SAR can evolve into PAR [7], as symptoms worsen following exposure to seasonal and perennial allergens.

Nasal itch, sneezing, rhinorrhea, and nasal obstruction, which are mediated by an elevation of IgE and mast cells, are the most common symptoms of AR. Thus, when a patient is exposed to an allergen, such as house dust mites, cockroaches, mold, or animal dander, IgE-sensitive mast cells degranulate and upregulate leukotrienes, cytokines, histamine, and prostaglandins, leading to the symptoms of AR [36].

Previous research reported that acupuncture and moxibustion are often effective treatments for AR [20, 37]. In fact, both treatments had been used thousands years ago, and WHO also listed 43 acupuncture and moxibustion-treated diseases, which included those of the respiratory system [38]. Moxibustion is believed to work by providing heat and chemical stimulation [39]. In TKM, AR is usually attributed to a deficiency of Wei Qi and wind and cold [40]. In agreement, modern medicine indicates that AR can be caused or aggravated by the cold air that occurs during winter and in the early morning [41]. The heat stimulation provided by moxibustion may thus account for its efficacy in treating AR [40]. Moxibustion also functions in immunomodulation through immunoglobulin, cytokines, and immune organs like the thoracic duct and spleen [42]. In particular, moxibustion can reduce the levels of interleukin (IL)-4, increase the interferon (IFN)-γ/IL-4 ratio, and reduce IgE-mediated inflammatory reactions [43].

Although moxibustion can provide clinical benefit to patients with AR, it is difficult to perform on the face due to the risk of burns and smoke inhalation. A recent study examined 814 patients who received TKM for AR and found that 72% received acupuncture but only 0.2% received moxibustion [24].

Electric heating moxibustion was recently developed to avoid the disadvantages of conventional moxibustion while maintaining its clinical benefits. The electric heating moxibustion device can automatically stop increasing the temperature when it reaches a critical level, thereby preventing burns and fire. In addition, electric heating moxibustion does not generate smoke or fine dust and thus does not cause respiratory discomfort. Electric heating moxibustion is also easier to implement and does not require an ignition system or an exhaust system. Most importantly, electric heating moxibustion can maintain an appropriate temperature and produce the same thermal stimulus as traditional moxibustion [44]. These many advantages are the reasons we assess the possibility of treating PAR with electric heating moxibustion.

There are several limitations of this trial. First, the number of participants (total 40) is insufficient for a clinical trial. However, our purpose at this time is to check the feasibility of using electric heating moxibustion for treating PAR. Second, it is difficult to blind both the practitioner and the participants, because the instruments used for acupuncture and electric heating moxibustion are very different. Therefore, we will attempt to reduce the bias by blinding an assessor who does not participate in the patient allocation assignment or the administration and practice of the treatment. Despite these limitations, this will be the first clinical study to examine the use of electric heating moxibustion for the treatment of AR.

### Trial status

The final protocol version is 1.3, dated 17 May 2018. The recruitment began on 23 May 2018 and is ongoing.

## Data Availability

Data and material from this trial are available upon reasonable request and approval by the corresponding author.

## Abbreviations

ANOVA: Analysis of variance
AR: Allergic rhinitis
CRA: Clinical research associate
CRF: Case report form
FAS: Full analysis set
ITT: Intention-to-treat
LOCF: Last observation carried forward
PAR: Perennial allergic rhinitis
PP: per-protocol
RQLQ: Rhinoconjunctivitis Quality of Life Questionnaire
SAR: Seasonal allergic rhinitis
TKM: Traditional Korean medicine
TNSS: Total Nasal Symptom Score
